#### Cost-effectiveness analysis

The cost analysis consists of two main parts. First, at patient level, volumes of care related to the CD care and anti-TNF therapy will be measured by means of the iMTA MCQ. This questionnaire measures all relevant healthcare related costs like outpatient visits at any medical specialist, hospitalisations and imaging procedures. Loss of productivity due to illness or recovery in patients below the age of 65 years will be estimated based on patient reported absences from paid (or unpaid) labour measured with the PCQ. The second part of the cost analysis consists of determining the cost prices for each volume of consumption. The standard cost prices from the ‘Dutch Guidelines for Cost Analyses’ and www.medicijnkosten.nl will be used. For units of care where no standard prices are available real costs prices will be determined on the basis of full cost pricing. Productivity losses will be valued by means of the friction cost method. In the end volumes of care will be multiplied with the cost prices for each volume of care to calculate costs. Because we anticipate non-inferiority of the dose reduction strategy, we will primarily analyse cost-savings: direct medical cost as well as total costs (medical and non-medical costs) will be compared between intervention and control group. A possible small but acceptable loss of effect can be incorporated in the analyses by determining a decremental cost-effectiveness ratio (DCER) by dividing the difference in costs by the difference in QALYs between the groups. The DCER expresses with how much money a loss of one QALY is compensated. If this amount is high the decision makers may be willing to accept a loss of effect. Uncertainty in the DCER will be non-parametrically determined using bootstrap techniques (1000 replications). Results from this analysis will be presented in a scatter plot and willingness to pay (or accept) curve. Furthermore, the Net Monetary Benefit per patient will be calculated for different levels of willingness to accept (WTA) in euro’s per QALY, using the formula: WTA×effect (difference in QALY)−costs. This results in the net amount of money saved, when the possible loss of QALY is corrected for, using different WTA levels per QALY.

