## Background

Crohn’s disease (CD) is a chronic inflammatory disease of the gastrointestinal tract, characterised by a relapsing and remitting disease course. Patients show an abnormal mucosal immune response, resulting from an interplay of genetic susceptibility, environmental factors and the intestinal microflora.^1^ Treatment consists of immunosuppressive medication, including monoclonal antibodies that block tumour necrosis factor alpha (anti-TNF); such as infliximab, adalimumab and certolizumab. Adalimumab is a humanised anti-TNF antibody that is effective as both induction and maintenance therapy for CD.^2–4^ Adalimumab is administered by subcutaneous (sc) injection and an induction dose of 80 mg (week 0) and 40 mg (week 2) or 160 mg (week 0) and 80 mg (week 2) are generally used, followed by 40 mg every 2 weeks.^5^

Although adalimumab is generally safe, side effects do occur. The risk of (opportunistic) infections is increased, especially in combination with immunosuppressive therapies, most often thiopurines or methotrexate.^6–9^ A recently published review on long term safety of adalimumab (n=3606 CD patients) showed a high absolute risk of any infection of 119 events per 100 patient years (PYs) and a risk of serious infection of 6.7/100 PYs in this selected trial-population with relatively low comorbidity.^10^ The incidence rate of injection site reactions (local pain and swelling) was 7.7/100 PYs.^10^ In addition, several reports show an increased risk of skin cancer (both melanoma and non-melanoma skin cancer), especially in combination with thiopurines.^6 7 9 11 12^ In addition to potential side effects, the costs of adalimumab are significant. Before the introduction of biosimilars, the costs of anti-TNF in the Netherlands were €15 000–30 000 per CD patient annually.^13 14^ Anti-TNF including adalimumab is expected to continue to be the main cost driver of CD management for several reasons. First, the number of CD patients is increasing in the Netherlands.^15^ Second, recent data stimulate an early use of anti-TNF with an accelerated step-up or top-down approach in combination with treat-to-target (mucosal healing), to prevent bowel damage.^16^ Third, the entry of lower cost biosimilars will possibly cause physicians to preferentially prescribe anti-TNF treatment, which will increase its use.^17–19^

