### Secondary objectives

To report the proportion of patients that had successful interval lengthening, defined as the absence of a disease flare, while treated with adalimumab ETW or every 4 weeks (EFW), at week 48.To identify factors that are associated with successful interval lengthening (eg, baseline patient and treatment characteristics, FC, CRP, adalimumab drug levels and antibodies to adalimumab).To compare the cumulative incidence of patients with a transient flare (duration ≤8 weeks) between the intervention and control group at week 48.To compare the proportion of patients that used budesonide, prednisone or other immunomodulators in order to treat a (transient) flare.To compare the proportion of patients in clinical and biochemical remission between the intervention and control group at week 48. Remission is defined as an HBI <5, FC <150 µg/g and CRP <10 mg/L. In case disease activity is assessed with endoscopy or MRI scan, that conclusion overrules our definition.To compare inflammatory bowel disease (IBD)-specific quality of life by the Short-IBD Questionnaire (SIBDQ)) between the intervention and control group every 12 weeks during follow-up.To compare disease activity by HBI and patient reported outcome (PRO-2) between the intervention and control group every 12 weeks during follow-up.To compare medical consumption (by institute for Medical Technology Assessment (iMTA) Medical Consumption Questionnaire (MCQ)) and work productivity (by iMTA Productivity Cost Questionnaire (PCQ)) between the intervention and control group until week 48, in order to calculate the decremental cost-effectiveness ratio of this interval lengthening strategy.To compare the rates of (serious) adverse events ((S)AEs) that are (possibly) related to adalimumab and the rates of (S)AEs that are (possibly) related to adalimumab interval lengthening between the intervention and control group, expressed as events/100 PYs of follow-up.To compare adalimumab use between the intervention and control group, including the cumulative dose during follow-up, the proportion of patients that uses adalimumab ETW and EFW.

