### Assessments

Enrolled patients will visit the outpatient clinic every 24 weeks. If preferred by the patient or treating physician, the evaluations at week 12 and 36 can take place as outpatient clinic visit as well. Every 12 weeks, laboratory tests (eg, FC, CRP, haemoglobin and albumin) will be performed. At week 0, 24 and 48 serum samples are stored for measurement of adalimumab drug levels and antibodies to adalimumab. Additionally, patients in both arms will be interviewed via telephone every 6 weeks in between clinical visits to assess for adverse events, symptoms and potential disease activity. If such an interview suggests a disease flare, patients must visit the outpatient clinic in order to undergo complete disease activity assessment and laboratory and FC tests. If patients have a flare at week 48, disease activity will be monitored until disease remission, in order to define the flare as persistent- or transient flare. In addition, study questionnaires are automatically sent via Castor every 12 weeks. During follow-up, patients register the adalimumab injection dates in a study-diary and bring this to the outpatient clinic every visit to evaluate adherence to adalimumab. An overview of all visits and assessments is depicted in table 1 and figures 1 and 2.

**Table 1 T1:** SPIRIT schedule of enrolment, interventions and assessments

	Study period											
	Enrolment	Allocation	Follow-up									Extra
Timepoint	−t_1_	0	w_0_	w_6_	w_12_	w_18_	w_24_	w_30_	w_36_	w_42_	w_48_	w_e_
Enrolment												
Eligibility screen	X											
Informed consent	X											
Allocation		X										
Interventions												
*Intervention: lengthening adalimumab dosing interval*											
*Control: adalimumab every other week*												
Assessments												
*Medical history*	X	X										
*Laboratory tests**			X		X		X		X		X	X
*Faecal calprotectin*			X		X		X		X		X	X
*Storage of serum samples*			X				X				X	X
*Concomitant medication*			X	X	X	X	X	X	X	X	X	X
*(Serious) adverse events*			X	X	X	X	X	X	X	X	X	X
*Physician global assessment*			X	X	X	X	X	X	X	X	X	X
*HBI*			X		X		X		X		X	X
PRO-2, *IBD-Q and EQ5D*			X		X		X		X		X
*iMTA MCQ, PCQ*			X		X		X		X		X

*Haemoglobin, leucocytes, thrombocytes, albumin, C-reactive protein.

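### The cost analysis takes adalimumab volume from a 12-weekly questionnaire, although a diary of injection dates is already collected and could supply one count for both costs and cumulative dose

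*Protocol article*

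**What the plan says.** All references are to the protocol article.

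- **Source of volume.** Under Cost-effectiveness analysis, "volumes of care related to the CD care and anti-TNF therapy will be measured by means of the iMTA MCQ". The section then describes the instrument: "This questionnaire measures all relevant healthcare related costs like outpatient visits at any medical specialist, hospitalisations and imaging procedures". None of these examples is a count of drug doses.
- **How volume becomes cost.** The same section says that "volumes of care will be multiplied with the cost prices for each volume of care to calculate costs", and that "we will primarily analyse cost-savings: direct medical cost as well as total costs (medical and non-medical costs) will be compared". It also names a medicine-price website among its price sources, so drugs are costed here.
- **Timing of the questionnaire.** Under Assessments, "study questionnaires are automatically sent via Castor every 12 weeks". Table 1 places the iMTA MCQ at weeks 0, 12, 24, 36 and 48.
- **The diary.** Also under Assessments, "patients register the adalimumab injection dates in a study-diary and bring this to the outpatient clinic every visit to evaluate adherence to adalimumab". No other use is given.
- **Dose as an outcome.** The last of the Secondary objectives is "To compare adalimumab use between the intervention and control group, including the cumulative dose during follow-up". No data source is named for it.
- **Weight of the drug in total cost.** The Background states that "Anti-TNF including adalimumab is expected to continue to be the main cost driver of CD management for several reasons".

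**The concern.** The two strategies differ by design in how many injections are given. Cost is volume times price, so any error in the injection count passes straight into the cost difference, and from there into the decremental cost-effectiveness ratio and the Net Monetary Benefit. The plan assigns this count to a periodic questionnaire that it describes through visits, admissions and imaging. A dated record of the same quantity is kept for another purpose.

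Intervals in the intervention arm can also change between questionnaires. Figure 1 allows a flare to start at any time, and Step 3 of the Intervention group section allows a shorter interval after a confirmed flare or at the patient's wish. Dated entries place such a change exactly, whereas a 12-weekly form has to summarise it.

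There is also a question of consistency. If cumulative dose is later computed from the diary and costs from the questionnaire, the trial could report two adalimumab volumes for the same patients with no rule for which one stands.

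**Working it through.** The plan gives no figure for injection volume, so there is none to reproduce. The sample size does not depend on this point. The check is how large a counting error would be relative to the quantity being measured.

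**Inputs from the document**
- Follow-up: 48 weeks (Intervention group).
- Control interval: 2 weeks (Control group).
- Intervention interval: 3 weeks to week 24, then 4 weeks for patients in remission (Intervention group, Steps 1 and 2).
- Anti-TNF cost before biosimilars: EUR 15 000 to 30 000 per patient per year (Background).

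**Scheduled injections, full adherence and no flare** (weeks divided by interval)
- Control: 48/2 = 24.
- Intervention: 24/3 + 24/4 = 8 + 6 = 14.
- Maximum difference: 24 − 14 = 10, or 10/24 = 42% of control use.
- If the intervention arm stays at 3 weeks throughout: 48/3 = 16, a difference of 8 (8/24 = 33%).

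Per 12-week questionnaire window the schedules give 12/2 = 6, 12/3 = 4 or 12/4 = 3 injections.

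**Effect of a counting error.** An error of one injection per patient in one arm's mean, over the whole 48 weeks, is 1/10 = 10% of the maximum difference, or 1/8 = 12.5% of the smaller one. The next table rests on assumed net errors per 12-week window in one arm, over four windows. The document gives no error rate.

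| Assumed net error per window | Over 48 weeks | Share of 10 | Share of 8 |
|---|---|---|---|
| 0.25 | 1 | 10% | 12.5% |
| 0.5 | 2 | 20% | 25% |
| 1 | 4 | 40% | 50% |

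**In money.** Assume that the Background's anti-TNF range applies to adalimumab every 2 weeks. The cost for 48 weeks is the annual cost × 48/52, spread over 24 injections:
- 15 000 × (48/52)/24 = EUR 577 per injection.
- 30 000 × (48/52)/24 = EUR 1154 per injection.

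The maximum drug saving of 10 injections is then about EUR 5 770 to 11 540 per patient. These are pre-biosimilar prices, so current amounts may differ. The percentages above do not depend on price.

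**Illustration for one patient.** A patient goes from every 4 weeks back to every 3 weeks at week 30 but is counted as every 4 weeks to week 48. Actual use is 18/3 = 6 and counted use is 18/4 = 4.5, so use is understated by 1.5 injections. This is one patient's error, not an arm mean. To move the arm mean by a full injection, 1/1.5 = 67% of the arm would need the same miscount.

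**The case against.** **The sentence may mean something narrower.** It could refer to care consumed around anti-TNF therapy, with the injections themselves counted elsewhere. The listed examples fit that reading, and nothing bars the cumulative-dose figure from the costing. The reading is possible but strained: the sentence names anti-TNF therapy, the section cites medicine prices, and no other source of drug volume is given anywhere. Even on this reading, the source of the main cost component would be left unnamed where the method is otherwise specified.

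**The questionnaire is not shown to be the worse instrument.** The document gives no recall period, item wording or accuracy data for it. The diary is also filled in by patients, and it is brought to clinic visits that are required only every 24 weeks (weeks 12 and 36 are optional). This stands. The preference for the diary is a methodological judgement: a dated entry per injection is the more direct count.

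**Stronger readings do not hold.** A reader might infer that the plan will overstate savings. The document supports neither a direction nor a size of error. A reader might also take a patient who returns from every 4 weeks directly to every 2 weeks at week 30, giving 18/2 − 18/4 = 4.5 injections, or 45% of the maximum difference. That skips a step: the Intervention group section sends patients back to the last interval that worked, and the interval before every 4 weeks is every 3 weeks. A shorter interval at the patient's wish is accepted, so other paths exist, but the example still describes one hypothetical patient. Finally, a reader might say that one unreturned questionnaire removes a quarter of a patient's volume. That is so only if missing is counted as zero, which the document does not say.

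**Conclusion.** The point holds as a worthwhile improvement to a stated method. The plan names a 12-weekly questionnaire as the source for the cost component that the intervention directly alters, keeps a dated record of the same quantity for adherence only, and leaves the source of the cumulative-dose outcome open. Each injection of error in an arm's mean is 10% of the largest difference that the schedules allow. If flares bring the true difference below 10, the same error weighs more.

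This rests on two assumptions: that the sentence on anti-TNF volumes covers the injections themselves, and that dated entries count injections more directly than a periodic form. It does not show that the planned saving is biased. The primary non-inferiority analysis and the sample size are untouched.

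**What to change.** In the Cost-effectiveness analysis section, name the source for adalimumab separately. Suggested wording:

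*Adalimumab volume is the number of injections dated in the study diary from week 0 to week 48. Where diary entries are missing, the iMTA MCQ or any recorded dosing-interval data is used. All other care volumes come from the iMTA MCQ. The same adalimumab count is used for the cumulative-dose outcome.*

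Add to the cumulative-dose objective that it uses this count, and to Assessments that the diary serves dose and costs as well as adherence. The article does not describe a case-report-form log of adalimumab intervals, so confirm what is recorded before relying on it to fill gaps.

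The cost is the wording and some data entry from diaries already collected. The downside is that the diary is patient-completed and may be incomplete, so the share of injections taken from the fallback source should be reported by arm. No patient procedure or treatment rule changes.

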### Planned data analysis

The primary outcome; cumulative incidence of persistent flares will be expressed as proportions in both groups. A CI for the difference between study groups will be determined (adjusted for comedication use at baseline using the Cochran-Mantel-Haenszel procedure, as this variable is used for stratification in the randomisation process).^37^ The upper limit of the CI will be compared with the non-inferiority margin. We will use both intention to treat and per protocol analyses, as the latter is considered the most conservative analysis for non-inferiority trials.^38^ Patients in the interval lengthening group are included in the per protocol analyses if they: lengthened the adalimumab interval at least to 3 weeks, regardless whether they returned to a preceding effective interval in case of a disease flare. Patients in the control group are included in the per protocol analyses if they: used adalimumab EOW without consistent interval lengthening, incidental postponement of an injection during infection or around holidays is allowed. Descriptive patient (and treatment) baseline variables will be summarised as means±SD, medians with IQRs or percentages, depending on the type of measurement. Gender, body mass index, age, prior medication for CD, disease duration, Montreal classification, IBD-related surgical history, comorbidity, inflammatory parameters including HBI, FC, CRP, adalimumab drug levels and antibodies to adalimumab will be reported.

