The secondary continuous outcomes HBI, SIBDQ, PRO-2, adalimumab drug levels and antibody levels at 48 weeks will be analysed by either Student’s t-test or Mann-Whitney U test depending on the type of distribution of the data. In addition, the course over time for several continuous outcomes measured at multiple time points (every 12 weeks) will be analysed using repeated measures analyses in which the outcome can be corrected for the baseline value of the specific outcome and potential confounding factors. The number of (S)AEs that are (possibly) related to adalimumab or to adalimumab interval lengthening will be reported as rates, defined as events/100 PYs of follow-up; details of these (S)AEs will be provided. In the intervention group, patient characteristics and clinical features will be analysed to predict a persistent flare. A prediction model will be developed and fitted using a univariable selection based on a p value <0.2 and a multivariable approach with backward selection. Predictive accuracy will be determined by the area under the receiver operating curve. A two-sided p value of <0.05 is considered statistically significant. All statistical analyses will be performed by using IBM SPS Statistics V.25.0.

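### The cost comparison and the DCER numerator are specified without week-0 cost or the randomisation stratum; adjusting for both would gain precision from data already scheduled (low priority)

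*Protocol article*

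**What the plan says.** Under Cost-effectiveness analysis, the protocol article expects non-inferiority and therefore says "we will primarily analyse cost-savings". The comparison itself is one clause: "direct medical cost as well as total costs (medical and non-medical costs) will be compared between intervention and control group". The DCER is formed "by dividing the difference in costs by the difference in QALYs between the groups", and the Net Monetary Benefit uses the same cost difference. On uncertainty it says "Uncertainty in the DCER will be non-parametrically determined using bootstrap techniques (1000 replications". No model, covariate or stratum is named at any of these steps.

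The baseline data are scheduled. In Table 1 (Assessments) the MCQ and PCQ are marked at weeks 0, 12, 24, 36 and 48, and the text adds that "study questionnaires are automatically sent via Castor every 12 weeks".

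Adjustment is stated elsewhere in Planned data analysis. The interval for the primary outcome is "adjusted for comedication use at baseline using the Cochran-Mantel-Haenszel procedure", because comedication is the stratification factor. For several continuous outcomes measured every 12 weeks, the article foresees "repeated measures analyses in which the outcome can be corrected for the baseline value of the specific outcome and potential confounding factors". Costs are not among the outcomes named in that paragraph.

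**The concern.** Cost-effectiveness stands beside non-inferiority in the stated aim, and the cost difference feeds every economic result: the saving, the DCER and the Net Monetary Benefit. The trial was sized on persistent flares alone, and no precision is given for costs. The smaller arm has 53 evaluable patients.

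Use of care and absence from work may persist within a patient who has a chronic disease. If they do, the week-0 questionnaires predict part of the follow-up cost, and leaving them out makes the interval wider than the data require. If the arms also happen to differ at week 0, part of that difference appears in the estimated saving. The week-0 values are scheduled but have no stated role in the cost analysis.

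Adjusting the QALY for baseline utility would not address this, because it leaves the cost difference unchanged.

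**Working it through.** **Inputs from the protocol article.** Sample size section: 15% persistent flares in the control arm, margin 15%, one-sided alpha 0.05 (z = 1.64), power 0.8 (z = 0.84), ratio 2:1, 105 and 53 evaluable patients, 10% drop-out, 174 in total. No cost SD is given, and no correlation r between week-0 and follow-up cost. Both are unknown, so results are in SD units and r is assumed over 0.1 to 0.7.

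**Step 1: the plan's own figure.** Taking 15% in both arms, control n = 0.15 × 0.85 × (1 + 1/2) × (1.64 + 0.84)² / 0.15² = 52.3, and intervention n = 2 × 52.3 = 104.6. This agrees with 53 and 105. Then 158 × 1.10 = 173.8, which gives 174. The arm sizes can be used as stated.

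**Step 2: precision of an unadjusted cost difference.** SE = SD × √(1/105 + 1/53) = 0.169 SD. The 95% half-width is 1.96 × 0.1685 = 0.330 SD.

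**Step 3: effect of adjusting for week-0 cost.** The adjusted SE is the unadjusted SE × √(1 − r²). The equivalent gain in patients is 1/(1 − r²) − 1.

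| Assumed r | SE ratio | SE reduction | 95% half-width (SD) | Equivalent extra patients |
|---|---|---|---|---|
| 0.1 | 0.995 | 0.5% | 0.329 | 1% |
| 0.2 | 0.980 | 2% | 0.324 | 4% |
| 0.3 | 0.954 | 5% | 0.315 | 10% |
| 0.5 | 0.866 | 13% | 0.286 | 33% |
| 0.7 | 0.714 | 29% | 0.236 | 96% |

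A simulation of 10,000 trials per r (105 versus 53) gave SE ratios of 0.954, 0.870 and 0.722 at r = 0.3, 0.5 and 0.7. The mean error of the unadjusted difference was 0.000 to 0.001 SD, so it is unbiased.

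**Step 4: allowing for cost that week 0 cannot predict.** Direct medical and total cost both include adalimumab. All patients enter on the same regimen, so prior adalimumab volume hardly varies and cannot predict use after randomisation. Suppose, as an assumption, that half the follow-up variance is of this kind. The effective correlation is then r × √0.5:

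- r = 0.3: effective 0.212, SE ratio 0.977, reduction 2%
- r = 0.5: effective 0.354, SE ratio 0.935, reduction 7%
- r = 0.7: effective 0.495, SE ratio 0.869, reduction 13%

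**Step 5: shift given an observed imbalance.** If the arms differ at week 0 by one SE (0.169 SD), the unadjusted estimate moves by r × 0.169 SD. That is 0.03, 0.05, 0.08 and 0.12 SD at r = 0.2, 0.3, 0.5 and 0.7. This is the same variance component that adjustment removes in Step 3, seen from one realised trial. The two must not be added together.

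**The case against.** The strongest reply is that the omission is read from silence. The article says only that costs will be compared; it does not call the comparison raw or unadjusted. It condenses a full protocol (version 3.3) that is not shown, and covariates for a secondary comparison are commonly left to such a document or to an analysis plan. This stands against any claim that the sponsor has ruled adjustment out. It does not remove the point. The economic paragraph goes as far as the ratio, the bootstrap and the Net Monetary Benefit formula, and the same section states adjustment for other outcomes. A method that uses scheduled data and keeps the estimand can be recommended whatever the cause of the silence. If a fuller document already adjusts, the sponsor need only say so.

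A reader might infer that the cost saving will be biased. The documents do not support this. Under randomisation the unadjusted difference is unbiased, and a valid interval already covers chance imbalance.

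A reader might also put a euro figure on the loss, or express it as a share of the drug saving. The documents give no cost SD and no r. Their price range is for anti-TNF treatment in general before biosimilars. Any such figure would rest on stacked assumptions.

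Further limits stand:

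- Low r is plausible. Entry requires at least 9 months of steroid-free remission, which narrows the spread of prior CD care.
- Stratification on comedication was justified by flare risk. The documents do not link it to cost, so the gain from that term may be small.
- Week-0 questionnaires are scheduled, which does not assure completion.
- The productivity part covers only "Loss of productivity due to illness or recovery in patients below the age of 65 years".

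**Conclusion.** The point holds as a cheap improvement, not as the correction of an error. As written, the main economic comparison and the DCER numerator are between-group differences with no baseline or stratum term, although week-0 MCQ and PCQ are scheduled and comedication is the stratification factor. The cost is lost precision, plus error conditional on whatever imbalance is observed.

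Its size cannot be fixed from the documents. The SE reduction ranges from about 0.5% to 29% over r = 0.1 to 0.7. The smaller values in Step 4 are the better guide for direct medical and total cost if much of the variance comes from adalimumab use after randomisation. The direction does not depend on these assumptions: with r near zero, a prespecified adjustment gains almost nothing and costs almost nothing. The primary non-inferiority analysis and the sample size are untouched, so the priority is low.

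**What to change.** Add one or two sentences to the cost-effectiveness analysis:

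- Estimate the mean differences in direct medical cost and in total cost by linear regression on arm, week-0 MCQ/PCQ cost and comedication (yes/no).
- Use week-0 cost only as a covariate and do not add it to follow-up cost.
- Refit the model within each of the planned 1000 bootstrap replications and take the interval from them.
- Carry the adjusted cost difference into the DCER and the Net Monetary Benefit.
- Report the unadjusted difference as a sensitivity analysis.

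No new data are needed, and the estimand stays the mean cost difference. The one small downside is that a simple rule is needed for missing week-0 questionnaires, for example mean imputation of the covariate. Fixing the choice in advance also prevents a later selection between adjusted and unadjusted results once an imbalance has been seen.
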